### Study population

The study population will comprise patients attending general practice, out-of-hours general practice and emergency departments with recent symptoms suggestive of TIA or minor stroke. The primary care physician will assess whether a diagnosis of TIA or minor stroke is probable or possible. The former group will be eligible for the trial. The latter group will not be eligible for the trial, but will be eligible for the diagnostic accuracy study.

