### Trial interventions

#### Intervention plus usual care group

Intervention group patients will be treated with additional secondary prevention medications, unless there are clinical contraindications, prior to referral to a specialist clinic. Treatment will comprise of dual anti-platelets, blood-pressure lowering medication, and simvastatin 40 mg. All patients will then be referred to a specialist clinic as per NICE guidelines (with the degree of urgency dictated by the ABCD2 score) [6].

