### Follow-up

There will be a 90-day follow-up clinic at the hospital. This will be supplemented by a review of GP and hospital records, flagging with the NHS Central Register and telephone contact or home visits for patients who do not or cannot attend the 90-day follow-up clinic. These follow-up mechanisms will:

• Confirm the final diagnosis.

• Record the patient’s blood pressure and serum cholesterol at 90 days.

• Identify primary and secondary outcomes.

• Monitor for serious adverse events and deaths.

• Record any changes in treatment and persistence with medication at 90 days.

• Collate cost data.

• Assess the patient’s quality of life at 90 days.

• Record side effects.

Prior to contacting participants for a follow-up, their health status will be established via their GPs to establish that they are not deceased and to ascertain whether their mental capacity has been lost. Participants identified as having lost capacity will be contacted and an appropriate consultee appointed. Detailed information about the trial will be provided to the consultee, and if in agreement an appointment will be made for the participant’s follow-up visit, at which the consultee must be present and must sign a declaration form to confirm their accordance.

Blood pressure and serum cholesterol readings taken at the 90-day follow-up clinic will be sent to the patients’ GP.

Where strokes are identified, anonymised copies of the relevant clinical information (from GP and hospital records, post-mortem reports, scan reports and so on) will be obtained and sent to an independent end-point committee, who will be blinded to treatment allocation. Independently of each other, the end-point committee will determine whether or not a stroke occurred, and if so, what sort of a stroke it was. Characterisation will include: ischaemic or haemorrhagic and disabling, non-disabling or TIA. Secondary outcomes will also include all vascular events, all major bleeding and deaths. Relevant clinical records will be scrutinised by an independent expert blinded to treatment allocation, who will determine whether or not a vascular event or major bleeding occurred, and what it was using standard case definitions. All hospital admissions will be scrutinised for possible adverse events and the clinical records sent to an independent expert for review.

We will follow up all patients, including those in the RCT and the diagnostic study.

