### Analysis

For the statistical analysis,baseline, TIA clinic and follow-up variables will be summarised by treatment group and overall. Categorical variables will be summarised by the number and percentage of subjects in each category. Continuous variables will be summarised using the mean, median, standard deviation, interquartile range and minimum and maximum values. For the main trial, logistic regression analysis of the primary and secondary outcomes will determine the efficacy of rapid drug treatment initiation after adjusting for the variables for catchment area, clinic type and ABCD2 score. Analysis will be according to the intention-to-treat principle and the treatment effect will be expressed as an odds ratio and its corresponding 95% confidence interval. The influence of missing data on the robustness of the findings will be explored in sensitivity analyses (replacement by last value, mean of series and multiple imputation). All statistical analyses will be pre-specified in a comprehensive statistical analysis plan, which will be agreed by the trial steering committee in advance of the final database lock.

Clinical outcomes will also be analysed according to the following sub-groups:

• Specialist diagnosis of non-TIA, TIA or stroke.

• Primary care physician’s diagnosis of possible or probable TIA.

• Specialist’s ABCD2 score.

• Primary care physician’s ABCD2 score (both as recorded by the minimisation hotline and the case report forms).

• Baseline therapy.

• Recruitment site by location (Birmingham, Cambridge or Oxford) and clinic type (out-of-hours general practice, daytime general practice or emergency department).

• First TIA or stroke versus recurrent TIA or stroke.

We will analyse the TIA versus minor stroke outcome rates in both RCT groups to exclude diagnostic bias.

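### Two outcome subgroups (specialist diagnosis, specialist ABCD2) are recorded after treatment starts and are open to bias as treatment contrasts; a third (possible v probable) has no randomised contrast in the pilot

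*Protocol article*

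**What the plan says.** The Analysis section introduces the list with "Clinical outcomes will also be analysed according to the following sub-groups". Three entries matter here: "Specialist diagnosis of non-TIA, TIA or stroke", "Primary care physician’s diagnosis of possible or probable TIA" and "Specialist’s ABCD2 score". The others are the primary care physician's (PCP's) ABCD2 score (hotline and case report form versions), baseline therapy, location and clinic type, and first v recurrent event. All of these are fixed before randomisation. The list does not separate the two kinds of variable, and does not say which entries are meant as treatment-effect analyses.

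On timing, the section on the intervention group says: "Intervention group patients will be treated with additional secondary prevention medications, unless there are clinical contraindications, prior to referral to a specialist clinic". Under Specialist clinic, the specialist records ABCD2, blood pressure and diagnosis at a later visit, usually within 7 days of symptom onset, or within 24 hours at higher risk. Hospital records can supply the diagnosis later still, and one task of the 90-day follow-up mechanisms is "Confirm the final diagnosis".

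On eligibility, Study population says of possible cases: "The latter group will not be eligible for the trial, but will be eligible for the diagnostic accuracy study".

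**The concern.** A subgroup treatment comparison keeps the protection of randomisation only if membership is settled before treatment can influence it. Two of the listed variables do not meet that condition. If allocation, or a stroke after randomisation, can alter the specialist's diagnosis or score, the arms within a stratum no longer hold comparable patients. The stratum with specialist-confirmed TIA is the one readers would trust most, so a false benefit or a hidden one there would carry weight in designing the main trial.

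The possible/probable entry raises a different problem. Taken as a treatment subgroup it has an empty stratum. Taken as a comparison of outcomes, it sets trial patients against patients who were never randomised and have no randomisation date.

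**Working it through.** **1. Order of events.** The PCP records features and certainty, randomises, then prescribes (Initial presentation sections). The clinic visit follows. Specialist diagnosis and specialist ABCD2 are therefore post-randomisation measurements; PCP ABCD2 is not.

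**2. Can allocation reach the label?**
- *Visibility.* Patients are asked to bring their medication to the clinic, and the specialist records persistence with it. Blinding is stated only for the adjudication of outcomes (Follow-up).
- *Blood pressure.* Background lists it as an ABCD2 component. The intervention arm is started on blood-pressure lowering before the clinic reading. A lower reading could place a treated patient in a lower-risk stratum than the same patient under usual care.
- *Intervening stroke.* No section limits the final diagnosis to information from before randomisation. The protocol itself says many patients have a stroke before seeing a specialist. Its TIA definition requires no acute infarction, so an infarct after randomisation but before imaging could move a patient from TIA to stroke.

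**3. Stratum sizes.** The plan's only related figure is its diagnostic precision of about ±10%. With 100 probable and 67 possible cases, predictive value 67% and sensitivity 80%: true positives 67, false positives 33, diseased 67/0.80 = 83.75, non-diseased 167 − 83.75 = 83.25. Half-widths 1.96·√(p(1−p)/n) are:
- sensitivity: 1.96·√(0.8·0.2/83.75) = 8.6%
- predictive value: 1.96·√(0.67·0.33/100) = 9.2%
- specificity: 1.96·√(0.6·0.4/83.25) = 10.5%

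This reproduces the plan's figure to rounding, and it is not in dispute. It implies about 67 v 33 randomised patients with and without a confirmed event (33.5 v 16.5 per arm if allocation is 1:1, which is assumed). By PCP certainty the split is 100 v 0.

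**4. Illustration A: stroke before clinic changes the label.** Assumptions, not pilot figures: all patients present with TIA; 10% control stroke rate (borrowed from a scenario in Background); a share f of control strokes occurs before the clinic; treatment cuts those by 80% and later strokes not at all; every pre-clinic stroke leaves the TIA stratum.

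At f = 0.5, control has 5% before and 5% after; treated has 1% and 5%. Whole-group OR = (0.06/0.94)/(0.10/0.90) = 0.57. In the TIA stratum the risks are 0.05/0.99 = 0.0505 and 0.05/0.95 = 0.0526, giving OR 0.96.

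| f | Whole-group OR | OR in TIA stratum | Same, if later strokes are also cut by 40% |
|---|---|---|---|
| 0.25 | 0.78 | 0.98 | 0.47 → 0.57 |
| 0.50 | 0.57 | 0.96 | 0.38 → 0.56 |
| 0.75 | 0.38 | 0.94 | 0.28 → 0.56 |

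The benefit largely vanishes from the stratum if the drugs act only before the clinic, and is partly masked if they also act later.

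**5. Illustration B: no treatment effect, labelling differs by arm.** Assume 67% true events with 10% stroke risk, non-events with no stroke risk, and a fraction r of treated non-events labelled TIA. Treated risk in the stratum = 0.067/(0.67 + 0.33r). At r = 0.1 this is 0.0953, OR 0.95; at r = 0.3 it is 0.0871, OR 0.86; at r = 0 the OR is 1.00. Under this route, bias arises only if labelling differs by arm.

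**6. Clock for possible cases.** Secondary outcome measures times outcomes from randomisation, with time from first symptoms listed only as something to explore. Possible cases have the second origin but not the first.

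**The case against.** The specialist's diagnosis is meant as the reference standard for the presenting event, which precedes randomisation. Follow-up lists confirming that diagnosis separately from identifying outcomes, and strokes go to a blinded committee. No section says that a later stroke recodes the presenting diagnosis. The authors also foresaw the issue: Analysis plans to compare TIA v minor stroke rates by arm as a guard against diagnostic bias. For ABCD2, the Specialist clinic section lists the score and blood pressure separately without saying which reading feeds the score, and the baseline version is already a subgroup. There is good reason to look at results by confirmed diagnosis, because the Discussion notes that non-TIA referrals threaten the main trial's sample size. Finally, this is a pilot, the odds-ratio regression is introduced for the main trial, and a full analysis plan is promised.

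Much of this stands. It rules out saying that the strata are biased; it does not close the routes described. An arm-wise comparison of rates can detect gross imbalance but cannot exclude bias, and it does not touch ABCD2 or the empty stratum. A reader might also infer that the possible v probable comparison cannot be made at all. The documents do not support that: possible cases are followed up for the same outcomes, so event rates can be described in about 100 probable and 67 to 70 possible cases. What is absent is a randomised contrast. Whether the main trial would admit possible cases is not settled here.

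**Conclusion.** The point holds in this form: specialist diagnosis and specialist ABCD2 are measured after treatment starts in an open comparison, so treatment contrasts within them are not protected by randomisation and are open to bias. Possible v probable has no randomised contrast in the pilot (0 of 100), and its main outcome clock is undefined for possible cases.

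The existence of the problem follows from the protocol's own sequence and eligibility rules. Its size does not. The odds ratios above show direction and plausibility under assumed event timing, assumed relabelling and a borrowed event rate. It would be tempting to count the pilot patients who would be misplaced, but the documents give neither the share of strokes before the clinic nor a recoding rule, and the fall from 10% to 2% is a national what-if. The ABCD2 effect is not quantified. The remaining subgroups are baseline factors and are unaffected.

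**What to change.** State which subgroups are treatment-effect analyses and limit those to pre-randomisation variables already listed: PCP ABCD2 as given to the minimisation hotline, baseline therapy, location and clinic type, and first v recurrent event. Use PCP ABCD2 in place of specialist ABCD2 for any treatment contrast. Keep specialist diagnosis only as an exploratory stratum, coded on the presenting event and disregarding anything after randomisation. Report possible v probable as a descriptive cohort comparison timed from first symptoms.

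The cost is analysis wording plus a coding rule for the presenting diagnosis; the baseline variables are already collected. The price is that results by confirmed diagnosis become exploratory only.

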### Ethical approval

The RAPID-TIA protocol was granted ethical approval by the Cambridgeshire 3 Research Ethics Committee (REC reference 11 EE 0040) and is compliant with the Helsinki Declaration.

## Discussion

The main aims of the RAPID-TIA pilot trial are to determine the feasibility of a randomised controlled trial, to analyse cost effectiveness and to ask: Should general practitioners and emergency doctors initiate secondary preventative measures in addition to aspirin in people they see with suspected TIA or minor stroke at the time of referral to a specialist?

While there are potential benefits of primary care initiation of treatment, potential adverse effects need to be considered. These include the risk of extension of haemorrhagic stroke from dual anti-platelet treatment, uncertainty about the effect of early statin treatment and unnecessary treatment due to overdiagnosis.

Anti-platelet agents decrease the risk of stroke and other cardiovascular disease but increase the risk of bleeding; both of these effects are increased by dual anti-platelet agents [22,23]. Although there is controversy over whether people experiencing a haemorrhagic stroke may have their stroke worsened by anti-platelet agents [24-27], it is reasonable to be alert to the possibility that dual anti-platelets may have a poorer prognosis if they are inadvertently given to a patient experiencing a haemorrhagic stroke. However, because ischaemic stroke is substantially more common than haemorrhagic stroke, it is currently standard practice to treat patients with TIA or minor stroke with a single anti-platelet agent (aspirin) before specialist review or brain imaging, on the basis that any delay in treatment will increase the risk of recurrent stroke [6]. Patients whose neurological symptoms have not substantially resolved are at higher risk of having had a haemorrhagic event, and therefore will be excluded from this trial. Haemorrhagic strokes occurring during the pilot or main trial will be recorded as significant adverse events.

There is currently no evidence that rapid administration of statin treatment is beneficial. The FASTER study investigated treatment with simvastatin 40 mg once daily versus a placebo in 392 patients within 24 hours of a stroke or TIA and failed to demonstrate whether this was either harmful or beneficial (the absolute risk increase of stroke within 90 days was 3.3%; the 95% confidence interval was −2.3% to 8.9%; *P*=0.25) [12]. However, there is evidence that statin treatment reduces the incidence of recurrent stroke in the long term in people who have experienced a stroke or TIA [28-30] and statin treatment is recommended for all patients who experience ischaemic stroke/TIA [6].

Approximately 50% of people referred to TIA clinics have not experienced a TIA or minor stroke [31]. Common alternate diagnoses include migraine, faints, vertigo and epilepsy [32]. It is therefore likely that this trial will increase the number of people who are given blood pressure treatment, statin therapy and anti-platelet agents for the brief period (usually less than 7 days) before they are reviewed by the specialist clinic. However, all these agents are commonly used in primary care to prevent cardiovascular disease, and it is unlikely that 1 to 7 days of unnecessary treatment will cause substantial harm – indeed, since clinicians use cardiovascular risk factors to assess the likelihood of TIA or minor stroke, many patients with alternative diagnoses may benefit from these drugs and the focus on their cardiovascular risk that a suspected diagnosis brings. Significant adverse events that occur prior to specialist clinic attendance will, however, be recorded.

Given that PCPs currently refer a high proportion of patients without TIA to TIA clinics (threatening to increase the sample size requirement), this pilot study will estimate the proportion of patients with TIA who are likely to be referred in the main trial, and gather evidence to support improved diagnostic accuracy in primary care. Currently diagnostic or referral support tools have not been trialled in primary care and as such there is no current evidence base to inform an intervention to improve the diagnostic accuracy of TIA referrals from PCPs. Within the pilot study, referring PCPs will have a choice as to whether to diagnose patients as probable TIA or minor stroke (and enter them into the treatment trial) or as possible TIA or minor stroke (and not enter them into the treatment trial). It is likely that this choice will mean that more than 50% of patients entered into the treatment trial will have experienced a TIA or minor stroke, and this pilot study will gather data on whether diagnostic accuracy is higher in the “probable TIA” group.

This pilot study will therefore both test the feasibility of the main study and provide novel data on diagnostic accuracy in primary care and the primary care recorded clinical features that are associated with a positive specialist diagnosis. The main study will inform national stroke prevention policy in patients with suspected TIA and contribute significantly to the evidence base for managing TIA in primary care.

The study so far has experienced some difficulties. Recruitment occurred in real time and this can prove difficult depending on the demands the PCP is experiencing at the time of recruitment, such as a late-running clinic. This led to patients meeting the inclusion criteria being missed. We are also experiencing low recruitment rates. To try to understand why this is occurring we are carrying out audits on the participating GP practices, as well as the participating TIA clinics, to enable us to quantify the reasons why patients were not recruited into the study.

## Trial status

The study started recruiting participants in November 2011, and recruitment closed 31 December 2012.

## Abbreviations

BP: Blood pressure; GP: General practitioner; NICE: National Institute for Health and Care Excellence; PCP: Primary care physician; RCT: Randomised controlled trial; TIA: Transient ischaemic attack.
